### Other measurements and adverse events

Basic social and demographic data, such as age, sex, marital status, place of living, housing characteristics, income, education and current and previous employments, will be collected from both the people with dementia and their informal caregivers. Information regarding alcohol use, smoking, physical exercise and diet of the caregiver will be retrieved using an ad-hoc module based on the forms of the Swedish National Health Survey.

The questionnaire developed for the study includes other instruments that have already been tested in studies addressing people with dementia. To assess the functional status of the people with dementia (dependency in both personal and instrumental activities of daily living (IADL)), the instruments of the interRAI suite will be used. As the full form of the RUD questionnaire will be administered, full information about use of health care services, medications, and other characteristics of the caregiving relationship will be available.

Although TECH@HOME is a nonpharmacological trial, the research team will actively monitor adverse events, i.e., any unfavorable and unintended sign, symptom, or disease temporally associated with the intervention, whether or not it is causally related to the study (e.g., falls, acute episodes of illness, etc.). This will mainly be done using two sources of information: (1) people with dementia and their caregivers will be instructed to refer to the clinical study coordinator in case of serious adverse events (requiring general practitioner support or hospital care) and (2) similarly, the clinical staff at the memory clinic will report in case any adverse event is acknowledged. Participants (both people with dementia and their caregivers) may be asked to withdraw if it is determined that participation in the trial does not represent the best interests of the participants themselves.

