**Fig. 1 Fig1:**
[figure not shown]
Standard Protocol Items: Recommendations for Interventional Trials (SPIRIT) figure of TECH@HOME

In the intervention group, besides usual care, the people with dementia will have a technological home monitoring kit installed in their home (as described under the “Intervention tested” section) while dyads in the control group will only receive usual care. Usual care for people with dementia in Southern Sweden can vary. In the target area, people with dementia usually receive comparable pharmaceutical treatment depending on the type of dementia, as prescribed by a general practitioner or a specialist at a memory clinic. Patients of memory clinics receive regular follow-ups depending on the type of diagnosis and on-going treatment response, while the majority of people with dementia are treated and monitored at a primary health care center and by the municipal health care services. Social workers from the municipality (“Biståndshandläggaren”) where the person resides, together with district nurses, have a meaningful role in tailoring the care plan by mediating access to other care services such as respite care homes, home help, and (dementia) nurse home visits. Use of such services depends on the specific needs of the person with dementia, which can also be unrelated to dementia, but rather dependent upon concomitant health and social issues.

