### Assessments and procedures for data collection

All participants signing the informed consent to participate will be enrolled in the study and will receive three home visits by a dementia nurse trained in the methodology used in the project. Informed consent will be actively sought both from people with dementia and their caregivers. In case of people declared legally incompetent, informed consent will be requested from a family member or from another person legally appointed by a judge to act as substitute. Home visits will occur at enrollment and after 3 and 12 months. Before the home visit, the self-administered sections of the questionnaires will be mailed to the caregivers participating in the study. The home visits will take approximately 1 h, during which the remaining sections of the questionnaire will be administered to the study participants and a general check of the self-administered forms will be made by the dementia nurse. Those in the experimental arm will receive the installation of the home monitoring kit at latest 1 month following the baseline home visit.

A 12-section study-specific questionnaire has been designed. The questionnaire sections addressing the people with dementia will be administered by the dementia nurse and cover the following domains: (A) sociodemographic information, (B) cognitive function, (C) ADL, (D) health and quality of life, and (E) use of health care resources.

The sections addressing the informal caregiver will be self-administered and cover the following domains: (F) sociodemographic information, (G) lifestyle, (H) health and quality of life, (I) mental health and wellbeing, (J) caregiver burden, (K) caregiving time, and (L) use of health care resources.

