### Handling of potential study bias

Risk of selection bias will be assessed by looking at the results of the enrollment process. Clinical staff will be instructed about how to explain, in very simple terms, what participation in the trial will entail. This is expected to reduce refusals among those people who are not very familiar with new technology. Considering the high level of “digital” education among the older population in Sweden, even compared to other Western countries, the likelihood of a selection bias should be minimized. The involvement of expert dementia nurses in the study also addresses the need to use research staff with a high level of know-how on how to relate with people with dementia and their families. This is also expected to reduce the dropouts and withdrawals during the study, thus increasing overall retention.

Other mediating and confounding variables might be associated with study outcomes, and these could lead to wrong/false results at the end of the trial. The use of a multidimensional questionnaire and the randomization process are expected to reduce such risks by providing several covariates that will be available for the statistical analyses to ensure the two study arms are comparable under several social, clinical and functional profiles.

Last but not least, the lack of adherence to the technology can constitute a major flaw for the study implementation and results. This risk will be minimized by using a standardized but thorough approach to the training of users (both people with dementia and their caregivers) with technologies, by using a very simple technological device, and by having the possibility to remotely monitor in real time the actual use of the devices. The study coordinator will be able to detect when a person is not using the technology and will promptly react in order to understand (and possibly address) the reasons behind the lack of use.

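### The adverse-event definition sets no observation window for controls, and its main reporting routes are reactive and may count events unequally between arms

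*Protocol article*

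**What the plan says.** The section *Other measurements and adverse events* promises that "the research team will actively monitor adverse events" and defines them as "any unfavorable and unintended sign, symptom, or disease temporally associated with the intervention, whether or not it is causally related to the study". It names two main sources:

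- Self-report: "people with dementia and their caregivers will be instructed to refer to the clinical study coordinator in case of serious adverse events". Serious here means needing a general practitioner's help or hospital treatment.
- The clinic: "the clinical staff at the memory clinic will report in case any adverse event is acknowledged".

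Three other places bear on this:

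- *Study design* says that "dyads in the control group will only receive usual care". In describing usual care in the area, it adds that "the majority of people with dementia are treated and monitored at a primary health care center".
- *Assessments and procedures for data collection* says that the experimental arm "will receive the installation of the home monitoring kit at latest 1 month following the baseline home visit".
- *Handling of potential study bias* says: "The study coordinator will be able to detect when a person is not using the technology". The coordinator then follows this up.

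**The concern.** An adverse-event definition in a two-arm trial needs a period of observation that means the same in both arms. This one is tied to an intervention that one arm never receives and the other receives after a delay. How control events, or kit-arm events before installation, are to be counted is left to whoever applies the rule.

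The method of collection adds to the difficulty. Reactive reporting depends on how often people are in touch with the study and on what they notice, and in an open technology trial both can vary with allocation. An observed difference in, say, acute illness could then reflect counting as well as harm or benefit. Falls and acute illness are the examples the protocol itself gives.

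**Working it through.** The article states no adverse-event rate or target, so there is no figure to reproduce. The check is a comparison of the text, followed by an illustration on assumed rates.

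**Step 1. The window, by arm and period**

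| Arm and period | Is there an intervention to be associated with? |
|---|---|
| Control, whole follow-up | No (usual care only) |
| Kit arm, baseline to installation | Not yet; this lasts up to 1 month |
| Kit arm, after installation | Yes |

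Only the last row has a clear window. The pre-installation gap is at most 1/12, about 8%, of a 12-month follow-up. The control gap is all of it.

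**Step 2. The two main routes, by type of event**

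| Event | Self-report to coordinator | Memory-clinic staff |
|---|---|---|
| Serious | All dyads, both arms | If staff learn of it |
| Non-serious | No instruction to report | If staff learn of it |

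Neither route asks a dyad anything, which sits badly with monitoring described as active. Non-serious events have only the clinic among the two named routes. *Screening and recruitment* recruits at the memory clinic but also sends brochures to primary health care centres. The clinic route may therefore miss non-serious events in participants who are followed elsewhere.

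**Step 3. What differs between arms**

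The reporting instructions do not differ. The surroundings do:

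- *Functionality of the kit*: kit-arm caregivers are alerted when the person leaves home or stays out of bed at night. *Eligibility criteria* allows the caregiver to live in another home, so some kit-arm caregivers may learn of events that a control caregiver would not.
- *Handling of potential study bias*: only kit dyads can be contacted about not using the devices.

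These are reasons why reporting may differ. They do not show that it does.

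**Step 4. Illustration on assumed values**

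Let p be the true 12-month event proportion, equal in both arms, and let rK and rC be the shares reported in the kit and control arms. The observed proportions are p·rK and p·rC, so the apparent risk ratio is rK/rC whatever the value of p. Take 160 per arm (*Sample size calculation and statistics*, with no dropout) and a two-sided 5% test of two proportions. The values of p, rK and rC are assumptions.

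| rK | rC | Apparent risk ratio | Chance of a significant false excess: p = 20% | p = 30% | p = 40% |
|---|---|---|---|---|---|
| 80% | 70% | 0.80/0.70 = 1.14 | 7% | 9% | 12% |
| 80% | 60% | 0.80/0.60 = 1.33 | 18% | 26% | 36% |
| 80% | 50% | 0.80/0.50 = 1.60 | 36% | 53% | 69% |

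For example, p = 30% with rC = 60% gives observed proportions of 0.30 × 0.80 = 0.24 and 0.30 × 0.60 = 0.18, or 38.4 against 28.8 expected reports. The direction (more reporting in the kit arm) is also assumed. The table shows that unequal reporting would matter if it occurred. It is not an estimate for this trial.

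**The case against.** The strongest reply is that harms are collected elsewhere, in both arms. Domestic accidents are a secondary outcome covering falls, minor injuries, wandering, burns, fires, flooding and other harmful events, recorded on a dedicated form. The full RUD questionnaire records health care use and medication. All dyads receive the same three home visits. This stands, and it rules out a conclusion that a reader might draw, that the arms cannot be compared on safety. It does not close the gap. The accident outcome concerns the person with dementia only and is not aimed at acute illness, and the RUD measures use of resources, not adverse events as such.

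Two other strong readings also fail. One is that collection differs by arm. The text applies both sources to everyone and says they are the main ones, so others may exist. Contact about non-use is not adverse-event collection, and the article does not say that the coordinator who makes it is the one who receives reports. The other is that participants followed in primary care are missed. Self-report of serious events covers every dyad and includes events that need a general practitioner, and the remark about the majority describes usual care in the area, not the trial sample.

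It can also be said that nobody would discard a control event, since the instruction to report goes to all participants, and that the article announces no between-arm analysis of these reports. The first is probably true of intent, but the control window stays undefined. The second limits the consequence to any comparison that is later made.

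Finally, a condensed article may leave visit questions to the full protocol. The absence of an adverse-event heading among the twelve questionnaire sections is therefore not held against the plan. The point rests on the definition and the sources that are stated.

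**Conclusion.** The point holds in limited form. Two things are firm from the text: the definition has no observation window for controls or for kit dyads before installation, and monitoring called active relies mainly on two reactive routes, with non-serious events left to one that may miss participants followed outside the clinic. It is a reasonable inference, not a stated fact, that reporting may differ by arm in this open trial. Adverse-event counts from these routes would therefore be hard to interpret between arms.

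The size cannot be established, because the documents give no event or reporting rates. The apparent risk ratios of 1.14 to 1.60 rest wholly on assumed reporting shares. The primary outcome is not affected.

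**What to change.** - Define an adverse event as any unfavourable event from randomisation to the month-12 visit, in both arms, regardless of kit use. Count that visit from the same point in both arms: *Study design* counts from enrolment, while the Abstract counts from installation, which controls do not have.
- Ask every dyad the same structured adverse-event question at the existing 3- and 12-month home visits.
- Base any between-arm comparison on that question together with the domestic-accident form, and treat spontaneous and clinic reports as supplementary.

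The cost is a sentence of wording and one short added question per visit, with no new visits. The question relies on recall over up to 9 months (month 3 to month 12), so mild events will still be under-counted, but both arms will have been asked in the same way.

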### Sample size calculation and statistics

According to Nordberg and colleagues [5], the mean number of hours spent in caregiving by informal caregivers of people with dementia ranges from 7.7 h per week (people with clinical dementia rating (CDR) 0.5) to 46.9 h per week (people with CDR 2.0). Wimo and colleagues [41] suggest that a standard deviation (SD) of 20 can be considered acceptable when using informal caregiving hours as an outcome for formal sample size calculation. Given these numbers, a sample size of 320 dyads randomized in a 1:1 ratio (160 per arm) is sufficient to detect a mean decrease in caregiving time of 1 h per day with a statistical power of 0.8 and a dropout rate of 20%, aiming at a final number of 128 dyads in the experimental arm and 128 dyads in the control arm.

The final database will be checked and cleaned using statistical routines after completion of each wave of assessments. All modifications made during this phase will be recorded in a specific file in order to allow for replicability of all operations made on the raw database.

All collected data will be made anonymous in accordance with the Swedish Data Protection Act (1998: 204) and coded in a database with access protection. The database will be stored on a server with continuous daily safety backup. Researchers will analyze data containing serial number encoded data without access to names or social security numbers. All information relating to the participants, the sampling framework, written consent, and the results from questionnaires are handled so that no unauthorized access to them can occur, and kept locked up. Only current researchers in the project will get access to the materials. Materials will be archived for 10 years.

The first step of the analysis will be exploratory in nature. A descriptive analysis of the sample will be conducted using univariate and bivariate statistical analyses with the aim of verifying the comparability of the study groups. Significant differences between exposures and outcomes will be compared using the chi-square test, Fisher’s exact test (in the case of categorical variables), the Mann-Whitney *U* test (for ordinal data such as the FES-I), the *t* test, or analysis of variance (ANOVA) test (for comparisons of continuous variables between groups according to a normal or non-normal distribution). Additionally, to check possible selection bias, the characteristics of the subjects in the sample will be compared, only on aggregate level, to those of the population with neurocognitive disorders included in the memory clinic register of the study area (e.g., age, sex, and place of living).

The primary outcome “time of informal care provided” will be compared between the two groups using analysis of covariance (ANCOVA). The analyses will be adjusted for variables which are nonhomogenously distributed in the two groups and controlling for other factors that the medical literature suggests are associated with the two outcomes (e.g., sex and age of caregivers, severity of dementia, and use of private care workers). The analyses of outcomes will be intention-to-treat (ITT).

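### The primary ANCOVA chooses some covariates by observed between-arm imbalance and does not name baseline caregiving hours; fixing both in advance gains power at no cost.

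*Protocol article*

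**What the plan says.** Primary outcome measurement (protocol article) defines the primary outcome as the change in weekly hours of informal care, measured with the RUD, from baseline to months 3 and 12.

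Sample size calculation and statistics begins the analysis with descriptive work and between-group tests intended to check that the arms are comparable. It then compares the primary outcome by ANCOVA, and states: "The analyses will be adjusted for variables which are nonhomogenously distributed in the two groups". The same sentence also controls for factors that the literature links with the outcomes. These are given as examples only: caregiver sex and age, "severity of dementia, and use of private care workers". No time of measurement is attached to them. Baseline caregiving hours are not named as a covariate anywhere in the article.

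Handling of potential study bias returns to the subject: "Other mediating and confounding variables might be associated with study outcomes". It expects randomisation and the many questionnaire covariates to reduce that risk by making the arms comparable.

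**The concern.** Part of the primary model is chosen by looking at which variables differ between the arms. In a randomised trial such differences are chance, and a difference does not make a variable worth adjusting for. What matters is how well the variable predicts the outcome. A strongly predictive variable that happens to be balanced is left out under this rule, and a weakly predictive one that happens to be unbalanced is brought in.

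No threshold for imbalance is given, and the candidates come from a 12-section questionnaire. The final model is therefore settled only after the arms have been compared, in a trial where one arm has visible equipment and the caregiver reports the outcome.

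The baseline value of the outcome is usually the most useful covariate for a change score. Here it is collected from everyone, but as written it is certain to enter only if it turns out unbalanced. At stake is precision that costs nothing, and a primary model that could be known in advance.

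**Working it through.** **Inputs from the article.** The sample is said to be "sufficient to detect a mean decrease in caregiving time of 1 h per day", that is 7 h/week. On variability, "a standard deviation (SD) of 20 can be considered acceptable when using informal caregiving hours as an outcome". The article gives power 0.80, 160 dyads per arm and 20% dropout, so 160 × 0.8 = 128 per arm analysed.

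**Assumptions.**
- Two-sided alpha 0.05. It is not stated, but it reproduces the sample size; one-sided 0.05 would need only 101 per arm.
- SD 20 is the SD of hours at one visit. The article does not say whether it refers to hours or to change.
- The correlation ρ between baseline and follow-up hours is not given. I use 0.5 to 0.7, with 0.3 as a low case.

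**Step 1: reproduce the plan.** n per arm = 2 × [20 × (1.960 + 0.842) / 7]² = 128.1. Power with 128 per arm is 0.7996. The stated figure stands, as an unadjusted comparison of two means.

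**Step 2: the two reference models.**
- Change score without baseline as covariate: SD = 20 × √(2(1 − ρ)).
- ANCOVA with baseline always included: residual SD = 20 × √(1 − ρ²). This is the same whether the dependent variable is change or follow-up hours.

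| ρ | SD, change | Power | Residual SD, ANCOVA | Power |
|---|---|---|---|---|
| 0.3 | 23.7 | 0.658 | 19.1 | 0.835 |
| 0.5 | 20.0 | 0.800 | 17.3 | 0.899 |
| 0.6 | 17.9 | 0.879 | 16.0 | 0.938 |
| 0.7 | 15.5 | 0.951 | 14.3 | 0.975 |

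**Step 3: the imbalance rule, by simulation.** The outcome is change, with 128 per arm. Baseline hours enter only if the arms differ on them at p < 0.05 (an assumed threshold).

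| ρ | Power, only if imbalanced | Power, always | Loss |
|---|---|---|---|
| 0.3 | 0.67 | 0.83 | 16 points |
| 0.5 | 0.80 | 0.89 | 9 points |
| 0.6 | 0.88 | 0.93 | 5 points |
| 0.7 | 0.95 | 0.97 | 2 points |

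The rule performs almost like no adjustment, because with a 5% threshold baseline hours enter in only about one trial in twenty.

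**Step 4: type I error.** Under this fixed rule it was about 4 to 5% in the simulations, at or slightly below nominal.

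None of these figures includes any other prognostic covariate.

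**The case against.** **The literature-based covariates enter regardless.** This is right: the imbalance clause is only half of the sentence. Dementia severity in particular is related to hours; the article's own figures run from 7.7 h/week at CDR 0.5 to 46.9 h/week at CDR 2.0. Such covariates can narrow the gap. As an illustration with follow-up hours as outcome, ρ = 0.6 and an assumed correlation of 0.5 between severity and hours, power is 0.91 if baseline enters only when imbalanced and 0.95 if always. How far this carries over to change is uncertain, since a covariate related equally to baseline and follow-up hours does not explain change.

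**An article condenses its covariate list.** This is partly right. The list is open, and nothing excludes baseline hours. But the imbalance rule is stated outright, and an analysis plan could cure it only by contradicting the protocol.

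**Three stronger readings do not hold.**
- A reader might infer that the trial is underpowered. The sample size assumes no adjustment, and the rule as written still reaches about 80% for correlations of 0.5 and above.
- A reader might infer a loss of 11 or 12 points at ρ = 0.6. That comes from taking follow-up hours as outcome and ignoring baseline (about 0.82 against 0.93). The primary outcome is change, for which the loss is about 5 points.
- A reader might infer that the analysis will adjust for consequences of treatment, because severity and private care are not tied to baseline and mediating variables are mentioned. Nowhere does the article say that follow-up values will be covariates, and the stated purpose, comparable arms, fits baseline values. It is a risk left open, not a plan.

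**Conclusion.** The point holds as a free improvement, not as a flaw that defeats the design. Choosing covariates by observed imbalance is a stated rule and a poor one, and baseline hours should be in the model whatever their balance.

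The cost of the present wording is about 2 to 9 points of attainable power at correlations of 0.7 down to 0.5, and about 16 points at 0.3. The planned 80% is missed only below a correlation of about 0.5. These figures rest on SD 20 being the SD of hours at one visit, on assumed correlations, on a 5% imbalance threshold, and on no other prognostic covariates.

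False positives are not increased under one fixed rule. What remains is the discretion left by an undefined threshold and an open list.

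**What to change.** In Sample size calculation and statistics:

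1. Delete the clause on adjusting for unevenly distributed variables. Baseline comparisons can stay as description.
2. State that baseline RUD informal-care hours are always a covariate in the primary ANCOVA.
3. Close the list of literature-based covariates (caregiver age and sex, dementia severity, use of private care workers) and say that each is taken at its pre-randomisation value.

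The third item also removes the open question about covariates that treatment could change. Adding cohabitation is optional.

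The cost is wording in the protocol and analysis plan, to be settled before the arms are compared. Caregiving time, cognitive function and sociodemographic data are already in the baseline questionnaire. The article does not name private care workers as an item, so the team should confirm that the baseline forms record it.
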